[18F]DCFPyL is a promising high-sensitivity second generation PSMA-targeted urea-based PET probe. Studies employing second-generation PSMA PET/CT imaging in men with biochemical progression after definitive therapy suggest detection of metastases in over 60% of men imaged.[3] In fact, PSMA-based PET has so far proven to have higher sensitivity than any other modality for localization of the site of recurrence. Applications that show promise and require further investigation include the characterization and risk stratification of primary PCa, complete staging of metastatic PCa to allow for PSMA-targeted radiotherapy and improved identification of patients with oligometastatic disease. One of the main advantage of this new PET tracer is that it is labeled with Fluor-18 instead of Gallium-68, which is the most commonly used ligand

in other PSMA targeted probes. The radionuclide F-18 has several physical advantages compared to Ga-68, including lower energy and shorter positron range providing higher image resolution, longer half-life (110min vs. 68min) enabling multiple scans from a single formulation, and shipment to other sites without radiochemistry/cyclotron capability.

Here we hypothesize that definitive RT informed by PSMA-PET findings will lead to improved cancer control outcomes compared with RT guided by conventional staging only. We will utilize a cmRCT design, where eligible patients will be randomly selected for PSMA-PET/CT imaging prior to RT and approached for this investigational study. This study will therefore be conducted in companion to PERA (Partnership initiative for the Evaluation of technological innovation in Radiotherapy, CHUM CER 17.032).

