## 6.0 Study Implementation

### 6.1 Study Design

6.1.1 Nested within the Partnership Initiative for the Evaluation of Technological Innovation in Radiotherapy (PERA - NCT03378856) prospective cohort, we will perform a Randomized Controlled Trial (RCT) comparing PSMA-guided radiotherapy (PSMAgRT) to controls.

When entering the PERA cohort, consent is asked for the use of data and for being approached for future research. Random selection of eligible patients to this trial were offered PSMAgRT. Outcomes will be compared with eligible patients randomized to a control arm and receiving usual care.

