#### 6.2.2 PSMA -PET/CT scanning

6.2.2.1 To be performed within 4 weeks of registration (or when PSA > 0.1ng/ml for patient post RP)

6.2.2.2 [18F]-DCFPyL PET/CT studies will be performed on hybrid PET/CT scanners which combine a dedicated, full-ring PET scanner with a multi-slice spiral CT scanner. Patients should fast for at least 4 hours to facilitate transit of oral contrast into the distal small bowel. A volume of 200-400 ml of barium sulfate oral contrast can be administered and  $9 \pm 1$  mCi ( $333 \pm 37$  MBq, calculated and decay-corrected) of [18F]-DCFPyL is injected by slow intravenous push followed by saline flush. 90 minutes (+/- 30 minutes)

following [18F]-DCFPyL injection, CT and PET images are consecutively acquired from the base of the skull to mid-thighs. Additional images of the skull, lower extremities or upper extremities might be acquired if there is a clinical suspicion of lesion at these sites. Repeat imaging of equivocal foci can be obtained up to 180 minutes post-IV. Optionally, Lasix 10-40 mg IV may be administered 30-60 minutes prior to primary or repeat imaging to help clear urinary bladder activity.

6.2.2.3 For the CT scan portion of the study, the following are suggested, (slight variation based on clinical sites' clinical routine is acceptable): 120-140 kVp, 60–140 mA (depending on the body weight or noise index), a rotation time of 0.8 s, a pitch of 1.75:1, and a detector row configuration using 0.625 mm thick detectors. For the PET portion of the study, a 3D acquisition is performed and images are acquired using 2-5 min per bed position (depending on the body weight and PET detector crystal composition) and 5 to 6 bed positions are used (depending on the patient's height). Non-stop-motion PET is also acceptable if the PET scanner has this feature. Time-of-flight imaging is encouraged if the PET scanner has this feature. PET attenuation-corrected, PET non-attenuation-corrected, CT, and fused images are available for review in the transaxial, coronal, and sagittal planes with an ordered subset expectation maximization (OSEM) or similar iterative algorithm for the PET images.

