6.2.2.4 The uptake of the lesions will be measured with SUVmax. SUVmax will be calculated using the usual formula with computations that also consider the post-injection residual activity. Patients will be weighed in the imaging department. Hepatic and blood pool SUV will be determined for the computation of tumor-to-liver and tumor-to-blood ratios.

6.2.2.5 Experienced central readers from each institution will adjudicate by consensus for each newly detected lesion beyond standard-care imaging. Disagreements between two experienced readers will be adjudicated by a tie-breaking third vote of a

195 separate nuclear medicine physician. Central review may result in  
 196 recommendation of MRI and/or biopsy of suspicious lesions.

197

198 6.2.2.6 Reports will be provided to treating physicians within 3  
 199 weeks of imaging.

200

201 6.2.2.7 Images will be provided if requested by treating physician  
 202 to assist in treatment planning.

203

204 6.1.3 Confirmation MRI: In cases where PSMA -PET/CT findings are  
 205 uncertain, an MRI of the questioned lesion site may be performed  
 206 at the discretion of the treating team.

207

208 6.1.4 Radiotherapy

209 6.1.4.1 PSMA -PET/CT imaging – no additional lesions detected: If  
 210 no additional lesions are detected, radiotherapy to  
 211 proceed as planned per standard care.

212 6.1.4.2 PSMA-PET/CT imaging – consistent with oligometastases  
 213 (1- 5 lesions): ALL oligometastatic lesions must be  
 214 treated with definitive radiotherapy. (see Guide –  
 215 Appendix 1)

216 6.1.4.3 PSMA-PET/CT imaging – consistent with widely metastatic  
 217 disease (>5 lesions): Treatment of all detected disease with  
 218 radiotherapy is not recommended. Physicians may alter  
 219 their radiotherapy plan as their discretion. However  
 220 treatment of the primary disease is encouraged.

221 6.1.4.4 RT summary to be provided (Impact of PSMA, Date  
 222 completed, Dose, Fractionation, Sites treated)

223

224 6.1.5 Hormonal therapy

225 6.1.5.1 At the discretion of the treating physician. However a  
 226 change in hormonal therapy is discouraged.

227

228 6.1.6 Follow-up

229 6.1.6.1 Per standard care practice / PERa, at least annually with  
 230 PSA and EPIC questionnaires.

231 6.1.6.2 Biochemical failures (Phoenix) to be investigated per  
232 standard care.

233 6.2 Withdrawal Criteria

234 Patients may be taken off study prior to the completion of study related  

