235 procedures for the following reasons:

236 6.2.1 Patient withdraws consent for participation.

237 6.2.2 It is deemed in the patient's best interest as determined by the  
238 attending/PI.

239 6.2.3 Serious protocol violation as determined by the PI

240 6.2.4 Development of a concurrent serious medical condition during the  
241 studies or treatments precluding completion of study procedures.

242 6.2.4 Completion of per-study follow-up (5 years after radiotherapy)

243 **7.0 Data collection and Confidentiality**

244 7.1. Hard Copies

245 6.1.1.1 Consent forms

246 7.2 Electronic Data

247 7.2.1 Medical records (Eg. EMR, OACIS, MOSAIC)

248 7.2.2 Imaging Data (Eg. Clinical PACS, Research PACS), including  
249 anonymized electronic submission for the research access use of 18F-  
250 DCFPyL imaging.

251 7.2.3 Research Data (Eg. Excel spreadsheet, Research PACS, Nuclear  
252 Medicine Reports, CASTOR EDC)

253 7.3 Confidentiality

254 7.3.1 In all research records, subjects will be identified by enrollment  
255 number.

256 7.3.2 Research data will be under secure password, or kept under lock  
257 and key in the research office.

258 7.3.3 No records bearing patients identification will be provided to  
 259 anyone outside of the institution except regulatory agencies.

260 7.3.4 Patients will not be identifiable as individuals in any publication or  
 261 presentation that may result from this study.

262 7.4 Data Safety and monitoring plan

263 7.4.1 PI will assume primary responsibility for monitoring the progress  
 264 of the trial and the safety of participants.

265 7.4.2 Data will be submitted to the REC annually for continuing review  
 266 and at the completion of the study per institutional guidelines.

267 **8.0 Study Endpoints**

268 8.1 Failure-free survival, defined as time to biochemical failure (Phoenix  
 269 definition, Roach 2006, or >0.2ng/ml for post-RP strata), local failure, regional  
 270 failure, distant metastases, initiation of the next line of therapy, or death  
 271 from any cause. (measured from end of RT) Event-free patients are  
 272 censored at their last known follow-up date.

273 8.2 CTCAE v5.0: Attributable Gr2+ toxicities.

274 8.3 Rates of biochemical failure, local failure, regional failure, distant failure, and  
 275 radiological failure.

276 8.4 Disease specific and overall survival

277 8.5 Health related quality of life: EPIC-CP, FACT-P, IPSS

278 8.6 Detection yield of PSMA-PET

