## 385 386 10.0 ETHICS

387  
388 10.1 The study will be submitted for initial and ongoing annual REB review.  
389 Study related procedures will not commence prior to receipt of REB approval.

390  
391 10.2 Any amendment to the study will be submitted for review by the REB  
392 before any changes are implemented unless required to eliminate immediate  
393 hazard to the study participants.

394  
395 10.3 Data derived from this study may be reported in scientific publications.  
396 Patients will not be indicated by name.

397  
398 10.4 Sample size determination

399 This study will employ a cmRCT design to determine the potential benefit of  
400 PSMA-PET guided radiotherapy in patient with high-risk of micro/oligo

metastatic disease. Patients will be randomly selected (1:1) for this intervention from the PERA study if they provide consent and meet eligibility criteria. The study will be designed with an  $\alpha=0.1$  and 80% power (as recommended for phase II randomized trials) for the primary outcomes. Patients will be stratified according to institution and category at time of enrollment (oligometastatic - estimated 15% of cohort) vs. high-risk localized – estimated 35% of cohort, vs. recurrent post RT – estimated 5% of cohort vs. recurrent post RP – estimated 45% of cohort).

Literature suggests that PSMA PET/CT can increase the diagnostic yield (sensitivity) for bone metastases by 10-15% compared with standard staging (approximately 85% to 99%), and for lymph node metastases by 50% (25% to 75%), resulting in over 60% of patient with high-risk of metastases demonstrating new identifiable lesions on PSMA PET. Adjusting for the proportion surviving free of failure at 5 years within the strata (0.05, 0.6, 0.3, and 0.4, respectively), a total of 130 patients receiving a PSMA -PET/CT evaluation (and 130 control) will be required to demonstrate benefit over standard care ( $\alpha=0.1$ ,  $\beta=0.8$ , one-tailed, HR 1.4).

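### Failure-free survival is timed from the end of RT, a date that follows random selection and that the PET can delay or remove in one arm only, so the arms need not be comparable at time zero

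*Protocol*

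**What the plan says.** **Origin.** Section 8.1 lists biochemical, local, regional and distant failure, next-line therapy and death as events, and starts the clock at the end of radiotherapy: "from any cause. (measured from end of RT) Event-free patients are" censored at last follow-up.

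**Order of steps.** The Introduction states that "eligible patients will be randomly selected for PSMA-PET/CT imaging prior to RT and approached for this investigational study". Section 10.4 gives the ratio: "Patients will be randomly selected (1:1) for this" intervention. Section 6.1.1 names the comparator: "Outcomes will be compared with eligible patients randomized to a control arm and receiving usual care".

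**What happens between selection and end of RT, in the PSMA arm only.**
- Scan (6.2.2.1): "To be performed within 4 weeks of registration (or when PSA > 0.1ng/ml for patient post RP").
- Report: "6.2.2.6 Reports will be provided to treating physicians within 3" weeks of imaging.
- Central review (6.2.2.5) may lead to a "recommendation of MRI and/or biopsy of suspicious lesions", with no time limit given.
- RT then follows the result (6.1.4). It goes ahead as planned if nothing new is found, and every lesion must be treated if there are 1 to 5. Above 5, the text reads "radiotherapy is not recommended. Physicians may alter" their plan. What is advised against there is irradiating all detected disease; the next sentence encourages treating the primary.

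The protocol gives no origin for a patient who never starts or finishes RT, and no rule for an event before the end of RT.

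**The concern.** A randomised comparison protects against bias when follow-up starts at a point that allocation cannot influence. Here it starts at a point the intervention can move or remove, in one arm. Suppose the PET shows widespread disease and the treating physician turns to systemic therapy without RT. That patient may have an event listed in 8.1 but has no date to measure it from. A control with the same, unseen, disease is irradiated as planned and enters the analysis. Separately, any death or progression between selection and end of RT falls outside the endpoint, and that window may differ in length between arms.

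At stake is the only primary test. It is already run at a lenient one-sided 0.10, and section 10.5 uses the same endpoint to choose strata for a phase III trial.

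**Working it through.** **1. Inputs.** From section 10.4: strata of 15/35/5/45%, 5-year failure-free proportions 0.05/0.6/0.3/0.4, one-sided alpha 0.1, power 80%, HR 1.4 (read as control/PSMA), 130 + 130 patients. From the synopsis: 3 years' accrual. From 6.2.2: up to 4 weeks to scan plus up to 3 weeks to report. Assumed, because the protocol gives no figure: exponential failure within strata unless stated otherwise, time from selection to end of RT, share of patients widely metastatic, and the fraction of those who end up without an end-of-RT date.

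**2. The plan's own figure.** Events = 4 × (1.2816 + 0.8416)² / (ln 1.4)² = 4 × 4.508 / 0.1132 = 159.3, so 160. With uniform 3-year accrual and 5 further years of follow-up, the mean event probability is 0.614, and 160 / 0.614 gives 261 against the stated 260. The sample size reproduces and is not the issue here.

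**3. Events that could fall before time zero.** The share failing within m months at the control rates is 1 − Σ(share × S₅^(m/60)).
- 2 months: 3.6%, about 5 of 130
- 3 months: 5.3%, about 7 of 130
- 6 months: 10.1%, about 13 of 130

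Over the 7 weeks allowed for scan plus report, the cohort figure is 2.9%. In the oligometastatic stratum it is 1 − exp(−0.599 × 7/52) = 7.7%, or about 1.5 of the 19.5 patients expected there (15% of 130). These are rough indications. They apply failure rates stated for follow-up to a period before RT ends, when Phoenix failure is not meaningful.

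**4. Effect of delay alone.** Null simulation: stratified log-rank, 260 patients, 4,000 runs, one-sided 0.10, 3-month base lead-in in both arms. The simulation standard error near 10% is √(0.1 × 0.9 / 4,000) = 0.5 points.
- Constant hazard, PSMA lead-in 1 to 6 months longer: type I error 10.0-10.8%, practically no bias.
- Rising hazard (Weibull shape 1.5), PSMA lead-in 1, 2, 3 or 6 months longer: apparent HR (control/PSMA) 0.97, 0.95, 0.93, 0.88; type I error 7.1%, 5.7%, 4.4%, 2.2%. This works against PSMA.

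**5. Effect of selective loss.** Null simulation, 130 per arm, 4,000 runs. A share of patients is widely metastatic, with the hazard the plan implies for the oligometastatic stratum. A fraction of them drops out of the PSMA arm only.

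| Widely metastatic | Quarter lost | Half lost | All lost |
|---|---|---|---|
| 3% | about 12% | 10.9% | 14.4% |
| 5% | about 12% | 13.2% | 15.9% |
| 8% | about 12% | 15.4% | 21.8% |
| 10% | about 13% | 16.2% | 26.1% |

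The columns come from separate runs, so small differences between them are noise. A second set of quarter-loss runs gave 10.5-12.5%, and repeats of the last column agreed within 2 points. With a tenth lost, the error is about 10-11%.

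A different construction agrees in kind. Dropping 10% or 20% of the earlier-failing half of the PSMA arm (6-7 or 13 patients), with a 1-month longer lead-in, gives 16% or 25%.

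**6. Origin at random selection.** Under the constant-hazard null the simulated type I error is 10.4%, nominal within simulation error. The event requirement does not change: 160 events, N about 261.

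**The case against.** The strongest case on the other side has five parts.

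- **Most patients will still have an end-of-RT date.** Section 6.1.4.3 encourages treating the primary even with more than 5 lesions. This stands. Losing every such patient is an upper bound, and a quarter or half is easier to defend.
- **No passage says that a patient without RT is excluded.** An SAP that is not shown could deal with analysis sets. True, but the origin itself is fixed in the protocol, and an analysis-set rule cannot supply a time zero that the definition does not give.
- **Delay does not favour PSMA.** This stands. Step 4 shows it to be neutral or adverse to PSMA.
- **The post-RP wait for PSA is largely empty.** This stands. Criterion 3.1.5.3 already requires PSA above 0.1 ng/ml after prostatectomy, so the point does not rest on that clause.
- **The 7 weeks are two upper limits added together.** Nothing says that RT in controls starts that much sooner, or that planning cannot run in parallel. This stands, so step 3 shows what could be uncounted, not a difference between arms.

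Timing from the end of RT is also familiar where both arms receive the same planned RT. Here RT is the thing the intervention changes.

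**Conclusion.** The point holds as a defect in how the primary endpoint is fixed. Time zero comes after randomisation and the PET can move or remove it in one arm, so the arms need not be comparable when the clock starts.

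Two stronger readings are tempting, and the document supports neither. A reader might infer that the trial is no longer randomised. Allocation remains random; what is not secured is comparability at time zero. A reader might also infer that the benefit of PSMA is inflated, with a type I error of 14-26%. That range needs every widely metastatic PSMA patient, and no control, to lose RT. The protocol states neither the share of such patients nor how many would go without RT.

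At a quarter or half loss the error is about 10-13% or 11-16% against a nominal 10%, and delay may pull the other way. The net direction is therefore unknown. All these figures rest on assumed inputs and on the plan's own stratum rates.

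**What to change.** In section 8.1, replace the origin and state the event rules once, identically for both arms:

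- FFS is measured from the date of random selection.
- All randomised eligible patients are analysed as allocated, whether or not RT is started or completed.
- Disease found at baseline staging, including the study PET, and the initial treatment course chosen before the end of RT are not failure events in either arm.
- Death or clinical progression after selection counts in both arms.
- Biochemical failure is judged on PSA after the initial treatment. Without this rule, recurrent patients admitted under 3.1.5.3 could meet the biochemical criterion at time zero.
- FFS from the end of RT is kept as a sensitivity analysis.

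The third rule must not be limited to changes triggered by the PET. Only the PSMA arm has those, so a limited rule would excuse events in that arm alone and favour it.

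Cost: a short paragraph in 8.1 and no change to the event requirement. The date of random selection has to be available for controls as well; the registry protocol is not shown, so this should be confirmed. FFS times lengthen by the planning and RT period. Patients who decline or do not receive the intervention stay in the PSMA arm and dilute the effect. This should be slight if most accept, but the protocol gives no acceptance rate, and section 10.4 counts its 130 as patients who receive the PET.

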## 9.2 Adverse Event Documentation & Reporting

### 9.1 Adverse event criteria

9.1.1 Toxicities will be evaluated and graded using CTCAE v5.0

9.1.2 Patients will be monitored for potential PSMA -PET-related or RT-related adverse events.

9.1.3 All adverse events of grade 2 or higher, whether serious or not, will be recorded if attributable to PSMA -PET/CT imaging or change in RT.

9.1.4 Any adverse event attributable to study intervention will be followed by the investigator until the event is resolved, the subject is lost to follow-up, the symptoms resolved, or the adverse event is found to be unrelated to the study.

9.1.5 An adverse event (AE) is any untoward, undesired, unplanned medical occurrence in a participant and does not necessarily have a causal relationship with the study intervention. An adverse event can therefore be any unfavourable and unintended sign (including an abnormal laboratory finding or physiological observations), symptom or disease temporally associated with the use of a medical treatment or procedure that may or may not be considered related to the medical treatment or procedure. Any symptom, sign, illness, or experience that develops or worsens in severity during the course of the study, including intercurrent illnesses or injuries, should be regarded as an adverse event.

9.1.6 Adverse events are classified as serious or non-serious. A Serious Adverse Event (SAE) is defined as any untoward medical occurrence/AE that:

9.1.6.1 Results in death;

- 361 9.1.6.2 Is life-threatening (refers to any adverse event that places  
362 the subject at immediate risk of death from the event as it  
363 occurred; life-threatening event does not include an event  
364 that, had it occurred in a more severe form, might have  
365 caused death, but as it actually occurred, did not create an  
366 immediate risk of death);
- 367 9.1.6.3 Requires in-patient hospitalization and/or prolongation of  
368 an existing hospitalization (hospitalization refers to an  
369 overnight admission). Emergency room visits are not  
370 considered serious until one of the above criteria is met.  
371 Any elective hospitalization for a pre-existing condition  
372 that has not worsened does not constitute an SAE;
- 373 9.1.6.4 Results in persistent or significant disability or incapacity  
374 (substantial disruption in a person's ability to conduct  
375 normal daily living activities); a congenital anomaly or birth  
376 defect; or other medically important event.

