### **2.2 Secondary objectives**

- 2.2.1 To determine acute and delayed toxicities.
- 2.2.2 To determine the rates of biochemical, radiological, local, regional, and distant failures, and time to next line therapy.
- 2.2.3 To measure prostate cancer specific and overall survival.
- 2.2.4 To measure health-related quality of life.
- 2.2.5 To measure the detection yield of PSMA PET/CT imaging.

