## **3.0 Eligibility Assessments**

### **3.1 Inclusion criteria**

- 3.1.1 Enrolled in PERa registry (CHUM CER 17.032), consented to contact for investigational trials, consented to serve as control, and randomly selected to be offered the experimental intervention.

- 3.1.2 Histological diagnosis of prostate cancer planned for definitive-intent radiotherapy.
- 3.1.3 ECOG 0-1
- 3.1.4 Charlson Cormobidity Index  $\leq 4$
- 3.1.5 High-risk of distant metastases as defined by any of:
- 3.1.5.1 Oligometastases ( $\leq 5$ ) (regional or distant) identified on conventional staging, with  $\leq 3$  metastasis in any non-bone organ. For a spine metastasis, direct involvement of adjacent spinal segments would still be considered as “one” tumour. For nodal metastases, more than one involved lymph node in the same ipsilateral nodal region/chain would still count as “one” tumour. Defined nodal regions for this protocol include inguinal, external iliac, internal iliac, common iliac, retroperitoneal, hilar/mediastinal, anterior cervical, posterior cervical, and axillary. Metastases in all other organs that are within 1cm of each other will be considered as “one” tumour.
  - 3.1.5.2 Subjects with newly diagnosed high-risk (NCCN) localized prostate cancer and CAPRA score 6-10.
  - 3.1.5.3 Subjects with a prior history of treated prostate cancer
    - Post-radical prostatectomy and biochemical failure ( $> 0.1\text{ng/ml}$ )
    - Post-curative radiotherapy and biochemical failure (Phoenix-RT)

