## 3.2 Exclusion Criteria

- 3.2.1 Prior androgen deprivation therapy terminated  $< 12$  months prior to enrollment.
- 3.2.2 Prior or planned PET scan.

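### Grade 2+ toxicity is recorded only when attributed to the PSMA-PET/CT or to a change in RT, so these records cannot support an unbiased between-arm comparison of CTCAE toxicity

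*Protocol*

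**What the plan says.** The relevant statements are spread over several sections of the Protocol. The numbering repeats: the adverse event items numbered 9.1.1 to 9.1.6 stand under heading 9.2.

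- **Objective 2.2.1** is unrestricted: "To determine acute and delayed toxicities".
- **Endpoint 8.2** reads "CTCAE v5.0: Attributable Gr2+ toxicities", without saying attributable to what.
- **9.2, item 9.1.2** sets wide monitoring: "Patients will be monitored for potential PSMA -PET-related or RT-related adverse events".
- **9.2, item 9.1.3** sets narrow recording: grade 2 or higher events, serious or not, "will be recorded if attributable to PSMA -PET/CT imaging or change in RT".
- **Study Design 6.1.1** states the comparison: "Outcomes will be compared with eligible patients randomized to a control arm and receiving usual care".
- **Eligibility 3.1.1** describes those who enrol under this protocol as "randomly selected to be offered the experimental intervention". **Exclusion 3.2.2** rules out "Prior or planned PET scan".
- **Radiotherapy 6.1.4.1 to 6.1.4.3**: RT is unchanged if the PET shows nothing new, all lesions are treated if there are 1 to 5, and the plan is at the physician's discretion if there are more than 5.
- **Follow-up 6.1.6.1** follows standard care or PERa, at least once a year, and names PSA and EPIC only.

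**The concern.** The experimental strategy can add irradiated sites. The Protocol accepts that this may cause side effects (the radiation-toxicity risk paragraph in section 9, and 9.3). Randomization offers an unbiased estimate of that net harm, provided toxicity is captured alike in both arms.

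Item 9.1.3 ties capture to exposures that only one arm has. Three consequences follow:

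- Background RT toxicity is left out in controls and in PSMA-arm patients with unchanged RT.
- The count in the remaining PSMA-arm patients depends on a causal judgement. The Protocol does not say who makes it and describes no blinding; PET reports go to the treating physicians (6.2.2.6).
- The rule works in one direction. If a PET result leads to a reduced plan, which 6.1.4.3 allows, the toxicity avoided cannot show up, because the control events it would be set against are not recorded.

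This is a data-capture rule, so no later analysis can recover grades that were never written down.

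**Working it through.** The plan states no toxicity rate by arm and no toxicity calculation, so there is no figure to reproduce. The check is a reading of the rules, followed by an illustration.

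**1. What is recordable under 9.1.3**

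| Patient group | PET trigger | Change-in-RT trigger | Ordinary RT toxicity recordable? |
|---|---|---|---|
| Control, usual care | none planned (3.2.2) | none | no |
| PSMA arm, RT as planned | yes, PET events only | none | no |
| PSMA arm, RT changed | yes | yes | only if attributed to the change |

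**2. How many patients**

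Inputs: 130 per arm and over 60% with new lesions on PSMA-PET, both from 10.4. The Protocol gives no rate of RT change. Assume exactly 60% have new lesions and all of them have changed RT.

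- RT changed: 130 × 0.60 = 78, which is 78/260 = 30% of all randomized patients.
- PSMA arm with RT unchanged: 130 − 78 = 52.
- Range: if 50%, 70% or 80% have changed RT, the unchanged group is 65, 39 or 26.

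**3. Recorded against true cases when the arms do not differ**

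The Protocol gives no control rate, so the true grade 2+ rate p is assumed equal in both arms. It is also assumed that control records arise only under 9.1.3. Events caused by the PET itself are ignored.

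| p | True cases per arm (130p) | Recorded, control | Recorded, PSMA arm, if every event in a changed-RT patient is attributed (78p) |
|---|---|---|---|
| 5% | 6.5 | 0 | 3.9 |
| 10% | 13 | 0 | 7.8 |
| 20% | 26 | 0 | 15.6 |
| 30% | 39 | 0 | 23.4 |

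Both arms are under-counted, by different amounts.

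**4. Chance of an apparent difference when there is none**

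Two-sided Fisher exact test of k/130 against 0/130: k = 5 gives p = 0.060 and k = 6 gives p = 0.029. Six recorded events are therefore enough to pass 0.05. The recorded PSMA-arm count is taken as Binomial(130, f × p), where f is the share with changed RT times the share of their events attributed.

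| Attribution in changed-RT patients | f | P(6 or more), p = 10% | P(6 or more), p = 20% |
|---|---|---|---|
| all | 0.6 | 80% | 99.9% |
| half | 0.3 | 20% | 80% |
| one in six | 0.1 | 0.2% | 5% |

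With identical true toxicity, the result swings from almost never to almost always different according to attribution practice. The comparison would measure the recording rule.

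**The case against.** The strongest reply is that 9.1.3 is a safety-reporting rule for the study intervention. It sits in the section on human subjects protection, next to an item on events attributable to that intervention. Controls are PERa cohort patients, followed under PERa, whose protocol is not shown and which may grade toxicity. Endpoint 8.2 does not limit attribution to the PET or to changed RT, so RT-attributable toxicity in both arms is a permissible reading. Objective 2.2.1 names no between-arm test. Monitoring more widely than one records (9.1.2 against 9.1.3) is not strictly a contradiction.

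Much of this stands, and it rules out stronger readings that a reader might infer:

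- **That the control toxicity rate is zero by construction.** The documents support only that none is recordable under 9.1.3; PERa may hold some.
- **That the toxicity objective cannot be answered at all.** Attributed PSMA-arm events can be described. EPIC is collected in follow-up, and EPIC-CP, FACT-P and IPSS are endpoints under 8.5, though as quality of life and not as CTCAE toxicity.
- **That all toxicity is lost in patients without new lesions.** Events attributable to the PET itself are still recorded.
- **That 52 of 130 is a bound.** More than 60% with new lesions would lower it. Patients with new lesions whose RT is left unchanged would raise it.

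The core point remains. This protocol names no CTCAE source for controls. Even if PERa grades toxicity, the PSMA-arm events recorded here would have passed an attribution filter that PERa's need not share. A SAP could define the analysis set, but it could not supply events that the protocol told sites not to record.

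**Conclusion.** The concern holds in a limited form. The CTCAE records made under 9.1.3 are asymmetric between arms and depend on attribution. They can support neither an unbiased between-arm comparison nor a total PSMA-arm rate of grade 2+ toxicity. The rule also fits poorly with the unrestricted objective 2.2.1, the stated comparison with randomized controls in 6.1.1 and the undefined attribution in 8.2.

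No control-arm RT toxicity is recordable under the rule, and about 52 of 130 PSMA-arm patients are in the same position under the assumption in the working. The probabilities there rest on assumed toxicity rates and show direction and sensitivity; they are not forecasts.

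The failure-free survival endpoint and its sample size are untouched. Because the loss affects a secondary objective, this should be fixed but does not undermine the trial's main conclusion. It is best done early, since acute toxicity is hard to reconstruct afterwards.

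**What to change.** Amend the Protocol so that 9.1.2, 9.1.3 and 8.2 state one rule:

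- Record every CTCAE v5.0 grade 2+ acute and late toxicity in both arms, on the same schedule and from the same sources, whether or not it is attributed to the PET or to a plan change.
- Name the source of control-arm grades. If it is PERa, apply the same PERa capture to the PSMA arm.
- Compare cumulative grade 2+ and grade 3+ incidence by randomized arm.
- Keep attribution to the PET or to changed RT as a separate descriptive field, and say who assigns it.

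The cost is a protocol amendment and modest extra data entry for controls. PERa consent already covers use of data (6.1.1), and medical records are already a data source (7.2.1); whether PERa covers toxicity abstraction needs checking. One limit remains: the only stated minimum is annual follow-up, so acute events may be under-captured where visits are no more frequent. With a common rule, that shortfall should at least be similar in the two arms.
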